## 8. Gas exchange

To evaluate changes, between arms, in gas exchange (as assessed by PaO2 mmHg, pCO2 mmHg, pH through ABGs)

[Time Frame: Last 10 minutes of 1h-trial]

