| 
several clinical parameters (i.e. DUS, EIT, ABGs, comfort, VAS) will be collected.
 
Specifically, Gas-flow rate will be set at a maximum of 60 L/min, temperature at a maximum of 37°C, while FiO2 will be adjusted to maintain a peripheral saturation (SpO2) between 92 and 98%.
                                                                                                                                                                                                                                                                                                                                      | 
a maximum of 37°C, while FiO2 will be adjusted to maintain SpO2 between 92 and 98%.
                                                                                                                                                                                                                                                                                                                                                                                                                                                                                                                                                                                       |

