| 
Active Comparator: Asymmetrical high flow nasal cannula (DUET HFNO)
 
After a 'baseline' trial using Venturi Mask, within the first 120 minutes after extubation, and assessing a PaO2/FiO2 ratio < 300 (as described above), patients will be randomly assigned to a second 1h-phase of 'DUET HFNO' vs 'conventional HFNO'. At the end of each session several clinical parameters (i.e. DUS, EIT, ABGs, comfort, VAS) will be collected.
 
Specifically, Gas-flow rate will be set at a maximum of 60L/min, temperature at a maximum of 37°C, while FiO2 will be adjusted to maintain SpO2 between 92 and 98%.
 | 
Device: Asymmetrical high flow nasal cannula (DUET HFNO)
 
After a 'baseline' trial using Venturi Mask, within the first 120 minutes after extubation, and assessing a PaO2/FiO2 ratio < 300, patients will be randomly assigned to a first 1h-phase of 'DUET HFNO' vs 'conventional HFNO'. At the end of each session several clinical parameters (i.e. DUS, EIT, ABGs, comfort, VAS) will be collected. Specifically, Gas-flow rate will be set at a maximum of 60 L/min, temperature at a maximum of 37°C, while FiO2 will be adjusted to maintain SpO2 between 92 and 98%. A 5-10min 'washout' phase using VM, between different interfaces, will be allowed.
 |

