## Eligibility

Minimum Age: 18 Years

Maximum Age:

Sex: All

Gender Based: No

Accepts Healthy Volunteers: No

Criteria: Inclusion Criteria:

- age >18 years old;
- invasive mechanical ventilation > 24h;
- acute respiratory failure within 120 minutes after extubation (defined during a spontaneous trial using Venturi mask and assessing a PaO2/FiO2 ratio < 300;
- absence of Sars-Cov-2 positivity;
- absence of cardiological or long-term respiratory disease

Exclusion Criteria:

- pregnancy
- tracheostomy
- non-invasive ventilation after extubation
- second tracheal intubation
- contraindications for EIT belt
- facial or nose abnormalities

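### The PaO2 part of the gas-exchange outcome is compared in mmHg while FiO2 is adjusted in both sessions to an SpO2 target, so it is confounded by FiO2; PaO2/FiO2 should be the oxygenation measure

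*Protocol*

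**What the plan says.** Under Outcome Measures, item 8 (Gas exchange) is defined as "To evaluate changes, between arms, in gas exchange (as assessed by PaO 2 mmHg, pCO 2 mmHg, pH through ABGs", with "Time Frame: Last 10 minutes of 1h-trial". PaO2 in mmHg is the only oxygenation measure among the eight listed outcomes.

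Under Arms and Interventions, the symmetrical cannula arm states that "FiO2 will be adjusted to maintain a peripheral saturation (SpO2) between 92 and 98" per cent. The DUET arm has the same rule: "FiO2 will be adjusted to maintain SpO2 between 92 and 98" per cent. The protocol does not say that FiO2 is kept the same in a patient's two sessions, or where within the band adjustment should stop. The same section allows a short Venturi-mask washout between interfaces but does not say whether FiO2 is carried across it.

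Study Design gives a randomised crossover with no masking and 20 patients enrolled. Study Status records the trial as completed.

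At entry the protocol does index oxygenation to FiO2: Eligibility defines respiratory failure by "assessing a PaO 2 /FiO 2 ratio < 300". That ratio does not return as an outcome, and FiO2 is not listed as one either.

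**The concern.** PaO2 depends on two things: how well the patient oxygenates on the interface, and how much oxygen is delivered. The second is adjusted in both sessions, towards the same saturation range, up to the time the blood gas is drawn. An interface that oxygenates better may then show a lower FiO2 instead of a higher PaO2. Two interfaces that oxygenate equally may show different PaO2 because staff, who can see which interface is in use, settled at different points in the band.

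Two wrong conclusions are possible. A real gain in oxygenation could be reported as no difference, or a difference in titration could be reported as an effect of the cannula. From PaO2 alone a reader could not tell which had happened.

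This is not a detail left to an analysis plan. The protocol itself fixes both the measure with its unit and the FiO2 rule under which it is taken.

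**Working it through.** The protocol gives no effect size, SD or power figure for this outcome, so there is no stated number to reproduce. What follows shows what can happen under stated assumptions.

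**Inputs from the protocol:** SpO2 band 92–98% in both arms; n = 20, each patient measured on both interfaces; PaO2/FiO2 below 300 at entry.

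**Assumptions:** normal dissociation curve (Severinghaus) with SpO2 equal to arterial saturation; set FiO2 equal to delivered FiO2.

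**1. Width of the band in PaO2.** With S = 1 / (23400 / (p³ + 150p) + 1):

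- S = 0.92 gives p = 63.8 mmHg
- S = 0.95 gives p = 75.7 mmHg
- S = 0.97 gives p = 90.6 mmHg
- S = 0.98 gives p = 104.2 mmHg

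The band is 104.2 − 63.8 = 40.4 mmHg wide. That is the extreme for one patient, not an expected mean difference. A systematic habit of settling at 97% on one interface and 95% on the other, both compliant, would shift the mean by 90.6 − 75.7 = 14.9 mmHg.

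**2. Could the trial register such a shift?** Detectable paired difference at 80% power and two-sided 5% (normal approximation) = (1.960 + 0.842) × SD / √20, where SD is that of the within-patient differences:

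- SD 5: 3.1 mmHg
- SD 10: 6.3 mmHg
- SD 15: 9.4 mmHg
- SD 20: 12.5 mmHg

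The 14.9 mmHg titration shift exceeds all four.

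**3. The reverse case.** Suppose PaO2 is 80 mmHg in both sessions, inside the band, with FiO2 0.40 on one interface and 0.50 on the other. Then 80/0.40 = 200, 80/0.50 = 160, and 200/160 = 1.25. Oxygenation is 25% better and the PaO2 difference is zero.

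**4. Dependence on how the FiO2 rule is applied.** Simulated paired t-tests used n = 20 and 4,000 runs, with PaO2/FiO2 of mean 200 and SD 45 and 8% within-patient noise. Three ways of following the rule were tried: FiO2 set afresh in each session to any point in the band; set afresh close to SpO2 95% (PaO2 SD 6 mmHg); or carried over and changed only when SpO2 leaves the band.

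| True PaO2/FiO2 gain | FiO2 practice | Mean PaO2 difference (mmHg) | Power, PaO2 | Power, PaO2/FiO2 |
|---|---|---|---|---|
| 10% | afresh, anywhere in band | 0.1 | 5% | 93% |
| 10% | afresh, near 95% | 0.0 | 5% | 94% |
| 10% | carried over | 6.6 | 93% | 94% |
| 20% | afresh, anywhere in band | 0.0 | 5% | 100% |
| 20% | afresh, near 95% | 0.0 | 5% | 100% |
| 20% | carried over | 11.8 | 100% | 100% |

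With no true gain, rejection was about 5% for both measures under all three practices. Systematically different titration between interfaces was not simulated; step 1 covers that case.

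Even with FiO2 carried over, the PaO2 difference is attenuated. Starting PaO2 averages (63.8 + 104.2)/2 = 84 mmHg, so at fixed FiO2 a 10% gain would give about 8.4 mmHg and a 20% gain about 16.8 mmHg, against 6.6 and 11.8 simulated. Power does not suffer there, because the band trims the noise as well.

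One limit: the simulation takes a patient's PaO2/FiO2 as independent of the FiO2 chosen, so the stability of the ratio across practices is built in. What it shows is how far raw PaO2 depends on a bedside habit that the protocol leaves open.

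**The case against.** A reader might infer that PaO2 cannot show an oxygenation difference, or that the whole gas-exchange outcome is held in range by the protocol. The documents support neither.

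- The target is a band, and the rule is to maintain SpO2 within it. That permits leaving FiO2 alone while saturation stays inside. Under that practice raw PaO2 does detect a 10% gain with about 93% power. The 5% result needs fresh titration in each session, which the protocol neither requires nor excludes.
- An SpO2 target does not hold pCO2 or pH. The Study Description rests the hypothesis on dead-space clearance and re-breathing, so pCO2 is arguably the gas-exchange measure closest to it, and it is untouched.
- This is one component of the last of eight outcomes. The primary outcomes, diaphragm ultrasound and end-expiratory lung impedance, do not depend on it, and the protocol ties no sample size or decision rule to PaO2.
- The dissociation curve, the SDs and the FiO2 example are assumptions. No stated figure is contradicted.

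All of this stands, and it limits the point to confounding of a single component. It does not remove it: the interpretation of PaO2 turns on FiO2, and FiO2 is not part of the outcome.

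**Conclusion.** The point holds for the PaO2 component of secondary outcome 8. Compared in mmHg while FiO2 is adjusted to SpO2 92–98% in both open-label sessions, raw PaO2 is confounded by FiO2 and cannot be attributed to the interface on its own. A true gain may be attenuated or show only as a lower FiO2. A difference of up to about 40 mmHg in one patient could come from titration alone. That size rests on the assumed normal dissociation curve; the power figures rest on the assumed PaO2/FiO2 distribution and noise.

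This should be fixed, but it does not threaten the trial's main comparison. It is also not a criticism of the saturation target: the issue is the measure read under it.

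**What to change.** Define the oxygenation component of outcome 8 as PaO2/FiO2 at the end-of-session blood gas, the index the protocol already uses for entry. Report the set FiO2 and raw PaO2 beside it for each interface, so that a reader can see whether a gain appeared as higher PaO2, lower FiO2 or both. Leave pCO2 and pH as they are. Clinical management does not change.

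The cost is small but not nil. FiO2 at the time of each blood gas must be available; the protocol does not list it among the parameters collected at the end of each session, so this has to be checked in the source data. Because the trial is completed, PaO2/FiO2 must be labelled as a measure adopted after completion, and the registered PaO2 comparison must still be shown. If FiO2 was not recorded, PaO2 should be reported with a statement that it cannot be separated from FiO2 titration.

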## Eligibility

Minimum Age: 18 Years

Maximum Age:

Sex: All

Gender Based: No

Accepts Healthy Volunteers: No

Criteria: Inclusion Criteria:

- age >18 years old;
- invasive mechanical ventilation > 24h;
- acute respiratory failure within 120 minutes after extubation (defined during a spontaneous trial using Venturi mask and assessing a PaO2/FiO2 ratio < 300;
- absence of Sars-Cov-2 positivity;
- absence of cardiological or long-term respiratory disease

Exclusion Criteria:

- pregnancy
- tracheostomy
- non-invasive ventilation after extubation
- second tracheal intubation
- contraindications for EIT belt
- facial or nose abnormalities

## IPDSharing

Plan to Share IPD:

References

Citations:

Links:

Available IPD/Information:
